Though integrated emergency care systems are considered a solution for providing accessibility to emergency care in diverse geographical settings, evidence based information for planning and implementing a patient centric integrated emergency care system, particularly in low resource settings, is required. Therefore, in the initial phase of the study we plan to conduct:(i) a systematic literature review: to synthesise evidence for an integrated emergency care system, which has been adopted globally or within India to meet the needs of the population served. This will provide an overview of what has been tried to be integrated and its purpose; how this can be used to develop the model, processes, strategies and structure within the context of the needs of the population of selected districts. (ii) health system readiness: a. health facility and pre-hospital (ambulance and helpline centres) resource and infrastructure assessment in the study district and a defined area in adjoining districts; b. Mapping of emergency care system: geo spatial mapping of facilities; mapping of current emergency care pathways, care processes and referral pathways using observation checklists, direct observation, and interview with health care providers; c. competency assessment of care providers and 1^st^ responders to assess the knowledge and skills of healthcare providers; d. budgetary provisions abstracted from administrative data including public and private insurance systems and; e. indicators of the current state of emergency care, e.g., hospital emergency visits, types of emergencies, patient outcomes.(iii) A community-based household survey: to estimate the burden of EMDs in the community and assess the health care services sought after the event. The survey data will provide information on the proportion who sought care, pathway of care & referral pathway, delay in seeking care, the expenditure incurred during care provision for the emergency medical condition and utilisation of insurance services. A multistage sampling strategy will be adopted. The study population will be stratified into urban and rural areas. Villages will be the primary sampling unit (PSU) in rural areas. Villages with a population of less than 500 will be excluded from the sampling frame, and villages with a population of more than 5000 will be split into clusters to have an approximate population of around 2000 in each cluster. In an urban area, census enumeration blocks will be a PSU. Sample size is calculated to estimate the burden of emergency medical conditions. Considering the burden of emergency conditions as 141/10000 population (Table 2), assuming a confidence level of 95% and a relative precision of 25% and design effect of one (design effect is considered as one as due to rarity of outcome the events are less likely to be clustered), the required sample size is 4292. Considering a non-response rate of 20% the sample size comes out to be 5365 which is further rounded off to 6000. A total of 60 PSUs will be randomly selected (PSU stratification for urban and rural will be based on district’s urban:rural distribution) and 100 households will be randomly selected from each PSU. All the individuals in the selected household will be included for the purpose of data collection.

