Evaluation will be done at baseline, concurrently during the implementation of the model and at the endline(S5 Table). Baseline, concurrent evaluations, and end-line survey data will be analysed to assess the feasibility, acceptability and the cost of the implementation of the model, and the effectiveness of the implemented model in terms of emergency care preparedness and coverage. Concurrent evaluation: Health facility assessment, qualitative interview with stakeholders, competency assessment of care providers will be done concurrently at an interval of three months. Post-care interviews (telephonically) of patients will be done to assess coverage and timeliness of care, expenditure, pathway of care, and delay in care. Endline evaluation: Endline survey will be conducted after the completion of the implementation phase. The sampling strategy and methodology of the endline survey will be similar to the baseline survey. Objective of the endline survey will be to estimate the increase in population coverage and health facility preparedness as compared to the baseline. The estimate of population coverage (i.e., reaching the appropriate health facility within a specified time frame as per the condition; this time frame will be decided during the formative research) obtained during the baseline survey will be used to calculate the sample size for the endline survey. Thus, the sample size for the endline survey will be calculated after the analysis of the results of the baseline survey. We are providing an illustration for sample size required for different scenarios of population coverage assuming a power of 80%, the confidence level of 95%, and a non-response rate of 20%. Thus, sample size included in baseline survey (at the district level) will be sufficient if there is at least 20% increase in population coverage from pre-intervention to post-intervention.

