#### Quantitative analysis.

The data will be duly checked for duplication, redundancies, missing values, and outliers. The key variables will be identified and summarized by measure of central tendency and measure of dispersion as per variable type. The incidence of emergency medical conditions will be calculated separately for urban and rural areas and pooled weighted estimates will be calculated based on distribution of population in urban and rural areas. The effect of the implementation model will be assessed statistically using appropriate methods as described here; We will perform the repeated measure Analysis of variance (ANOVA) as a univariate analysis for those dependent variables which are continuous in nature and having a within-subject correlation. The multivariate analysis for the same variables will be performed by linear mixed effect models (to account for population level and individual level variability). We further propose to calculate a population-average effect by Generalized Estimating Equations (GEE) looking at the structure of the data collection plan and robustness of GEE in the case of model misspecification. The temporal pattern (if any) in some variables will be checked by autoregressive integrated moving average (ARIMA) and if any temporal pattern is indicated we will perform a time-to-event analysis using Cox proportional hazard model.

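### Rarity does not justify a design effect of one, and the coverage sizing makes no clustering allowance; how much this matters depends on whether 6000 means persons or households

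*Protocol article*

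**What the plan says.** All figures are per district.

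- **Burden sizing (Formative research).** The expected burden is 141 per 10,000. The calculation proceeds by "assuming a confidence level of 95% and a relative precision of 25% and design effect of one", on the ground that "design effect is considered as one as due to rarity of outcome the events are less likely to be clustered". From this "the required sample size is 4292", and then "Considering a non-response rate of 20% the sample size comes out to be 5365 which is further rounded off to 6000".
- **Sampling (same section).** "A total of 60 PSUs will be randomly selected", with 100 households from each and every member of those households included. PSUs are villages (or parts of large villages) and census enumeration blocks.
- **Coverage sizing (Table 2 and the endline text under Secondary outcomes).** Table 2 lists the cases needed for baseline coverage of 10–40% and endline coverage of 20–80%. The stated inputs are 80% power, 95% confidence and 20% non-response. No design effect is named. The text concludes that the baseline sample is enough for a rise of at least 20%, which I read from Table 2 as percentage points.
- **Endline.** "The sampling strategy and methodology of the endline survey will be similar to the baseline survey"; its size is to be worked out after the baseline results.

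**The concern.** Rarity and clustering are different things. A low event rate may go with a low ICC, but the ICC is multiplied by the number of persons taken per PSU, and this plan takes many.

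The argument has no bearing at all on the primary outcome. Coverage is a proportion among people who had an emergency, and the protocol plans for 10–80%. Whether a case reaches an appropriate facility in time plausibly depends on the facilities, ambulances and roads that a village shares, and these are what the intervention sets out to change. Some within-PSU correlation should therefore be expected.

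Two planning statements are at stake: the 25% relative precision for burden, and the sufficiency of the baseline sample for a 20-point rise in coverage. The endline size is still open, so the assumption can be corrected before it is carried forward.

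**Working it through.** **1. Reproducing the plan's figures**

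Burden: n = z²(1 − p)/(r²p), with z = 1.96, p = 0.0141, r = 0.25 and a design effect (DEFF) of 1. This gives 3.8416 × 0.9859/(0.0625 × 0.0141) = 4298, against 4292 stated. Then 4292/0.8 = 5365, as stated.

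Table 2 cases: the two-proportion formula (two-sided 5%, 80% power, unpooled variance, continuity correction, no DEFF) reproduces all 13 rows after rounding up. For 20-point rises:

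| Rise | Formula | Table 2 |
|---|---|---|
| 10 to 30% | 68.5 | 69 |
| 20 to 40% | 88.2 | 89 |
| 30 to 50% | 100.0 | 101 |
| 40 to 60% | 103.9 | 104 |

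So neither sizing contains a clustering term.

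**2. The unit of 6000**

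The formula yields persons, but 60 PSUs × 100 households = 6000 households. The Abstract's 30,000 over five districts (6000 each) has no unit. Household size is not given; I assume 4, hence 24,000 persons. No ICC is given, so every ICC below is an assumption.

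**3. Burden**

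DEFF = 1 + (m − 1) × ICC. The 25% target holds while DEFF ≤ N/4292.

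| Reading | N | m per PSU | Largest DEFF | Largest ICC |
|---|---|---|---|---|
| Persons | 6000 | 100 | 1.40 | 0.0040 |
| Persons, 80% respond | 4800 | 80 | 1.12 | 0.0015 |
| Households | 24,000 | 400 | 5.59 | 0.0115 |
| Households, 80% respond | 19,200 | 320 | 4.47 | 0.0109 |

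Relative precision is 1.96 × √[DEFF(1 − p)/(pN)]:

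- Persons (N = 6000): ICC 0.005 / 0.01 / 0.02 gives DEFF 1.50 / 1.99 / 2.98 and precision 25.9% / 29.8% / 36.5%.
- Households (N = 24,000): the same ICCs give DEFF 3.0 / 5.0 / 9.0 and precision 18.3% / 23.6% / 31.7%.

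**4. Coverage, 20-point rises**

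Cases = 0.0141 × N. Because cases per PSU vary, I use DEFF ≈ 1 + (mean cases per PSU) × ICC. Power = Φ(d√[n₀/(p₁q₁ + p₂q₂)] − 1.96), where d = 0.20, q = 1 − p and n₀ = (√n − 1/(d√n))², which is the continuity correction that Table 2 uses.

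*Persons.* 6000 × 0.0141 ≈ 85 cases, or 1.41 per PSU. At ICC 0.1, DEFF = 1.14 and about 74 effective cases remain.

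| Rise | Table 2 needs | Power, 85 cases | Power, 74 effective |
|---|---|---|---|
| 20 to 40% | 89 | 78% | 72% |
| 30 to 50% | 101 | 72% | 66% |
| 40 to 60% | 104 | 71% | 64% |

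Only the 10 to 30% rise (69 cases) is covered, and not if 4800 respond (4800 × 0.0141 = 67.7 cases). Table 2's own population column agrees: it asks for 6692, 7594 and 7820 for the three rows shown.

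*Households.* 24,000 × 0.0141 = 338 cases, or 5.64 per PSU. ICC 0.1 to 0.3 gives DEFF 1.56 to 2.69, leaving 217 to 126 effective cases. With 19,200 respondents and ICC 0.3: 271 cases, DEFF 1 + 4.51 × 0.3 = 2.35, and 115 effective. All exceed the largest requirement of 104.

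**The case against.** The strongest reply is that the sampling rule which enlarges the cluster also enlarges the sample. Taking every member of 100 households yields several times the 4292 persons required. At 24,000–30,000 persons (4–5 per household) and ICCs of 0.001–0.005, relative precision is about 12–18%, inside the 25% target. The 20-point coverage claim also survives. This stands, and it limits the point: a reader might infer that the fielded survey's precision and power are overstated, but on the household reading the documents do not support that. The protocol does not claim this surplus as its margin, however, and leaves the unit unclear.

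Four other inferences should also be held back.

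- **Loss of power for 10-point rises.** The sufficiency statement covers only rises of at least 20 points, so weaker power for 20 to 30% does not contradict it.
- **Confidence intervals will be too narrow.** A planning design effect does not fix the analysis variance. Nothing says that PSUs will be ignored, and Quantitative analysis proposes GEE, though without naming the cluster. Survey variance may be left to a fuller document.
- **Weights are wrong.** The stated weighting is that "pooled weighted estimates will be calculated based on distribution of population in urban and rural areas". With equal-probability selection of PSUs and a fixed 100 households, selection chances would differ between small and large villages. But random selection of PSUs does not exclude selection proportional to size, so this is conditional.
- **The endline survey will be undersized.** Its size is still to be calculated and Table 2 is offered as an illustration. Nothing commits that calculation to a design effect of one.

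**Conclusion.** The stated sizing rule is wrong. Rarity does not justify a design effect of one with 100 or more persons per PSU, and it is irrelevant to a coverage proportion of 10–80%, which also gets no clustering allowance. At any positive ICC, 4292 and the Table 2 case numbers are too low as requirements.

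The effect on the survey actually fielded turns on one undocumented fact.

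- **Persons:** the 25% precision fails above an ICC of about 0.004 (0.0015 with 4800 respondents). Coverage power from baselines of 20–40%, already about 71–78%, loses roughly a further 6 points at an ICC of 0.1. Most of the shortfall below 80% at the higher baselines exists before clustering is considered.
- **Households, at an assumed 4 persons each:** the burden target tolerates a design effect up to about 5.6 (4.5 after 20% non-response), and the 20-point claim holds for coverage ICCs up to 0.3.

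The ICCs and household size are assumptions. The failure of the rarity argument does not depend on them.

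**What to change.** 1. Delete the rarity rationale and say whether 6000 per district (30,000 in total) counts persons or households.
2. Restate the 25% precision and the 20-point sufficiency statement with design effects above one, shown over a range of ICCs for each outcome.
3. Estimate the design effects for burden and coverage from the baseline survey. Use the coverage one in the endline calculation already planned; if the endline survey cannot grow, restate the detectable increase.
4. State that both surveys will be analysed with urban/rural strata and PSU as the cluster, and with weights from the actual selection probabilities if PSUs are not drawn proportional to size.

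Items 1, 2 and 4 are changes of wording and analysis, using PSU and household counts that sampling needs anyway. The price is a less favourable stated precision or detectable increase. Item 3 may mean a larger endline survey, with its fieldwork cost, if the sponsor chooses to hold power.

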### Development of provisional model ‘0’

A conceptual framework will be co-developed to frame the intervention framework involving the key stakeholders based on review, formative research and situational analysis. A co-design workshop will be conducted in each district under the leadership of the state government, attended by the research team, district program officers, community leaders, hospital managers, doctors, nurses, and paramedics from the participating hospitals and officials from non-health departments including transport, education and communication. The model will be co-developed based on the emergency care system framework and health system building block, encompassing community, prehospital and hospital care under various health system building blocks (e.g., infrastructure, equipment, supplies and provisions, financing, governance and leadership, information systems). Visual representation showing the description, relationships, and interactions with the different components in the provision of emergency care will be identified to co-develop the model. System-level and emergency medical disease-specific interventions will be developed and fine-tuned based on the workflows developed by the research team.

The core components of the provisional model will include (a) enhancing first aid at the community level, (b) strengthening prehospital care; (c) intervention strategies at the facility level; and (d) electronic and artificial intelligence-based decision support systems (Fig 3).

**Fig 3 pone.0331290.g003:**
[figure not shown]
Provisional model emergency care framework for co-development of Model ‘0’.

### Model optimization and development phase

Pilot testing of the model (M0) will be done in a limited sample and geographical setting which is likely to be representative of the entire district in consultation with the state. A single hub and spoke cluster will be chosen to have a representation of each level of health facility (prehospital care, Level 1, Level 2, Level 3, and Level 4) for each of the emergency conditions. Pre- and post-implementation data will be analysed to assess acceptability, feasibility and effectiveness based on process and quality outcome measures. Quantitative data on key indicators on the implementation strategy (e.g., effectiveness of training of care providers, appropriateness and effectiveness of educational materials), process indicators (e.g., adherence to new care protocols, patient satisfaction), and implementation measures (e.g., acceptability by the care providers) will be collected. The model will be refined based on a review of the provisional model, data collection and evaluation of the key indicators. As described in the formative research multi-stakeholder consultation (Co-design workshop), in-depth interviews and focus group discussions will be done to get further insights. Key areas will be identified where the provisional model has not worked effectively. Necessary adjustments will be made to the model in a consultative manner. Subsequent cycles will be developed by re-iterating the same process. A total of 3 iterative processes will be done to refine the model and to develop the final model (Px) (Fig 4). Each disease process will be deployed sequentially, and iterative processes and periods will be conducted accordingly. The threshold for initiating the scale-up phase will be decided during the formative research phase after the baseline surveys and mapping by the research team. The threshold will be multidimensional and the irrespective of attaining the threshold after 3 iterative cycles scale up will be initiated.

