### Scaling up of the final model

The piloted final model ‘Px’ will be scaled up step-wise to the entire district in a phased manner. The scaling-up sequence will start from the hub and spoke system where pilot testing was conducted and then progressively moved to the other spokes and other hubs of the district. A detailed scale-up strategy, tools to be used for scale-up and scalability of the model will be co-developed by consultation with the state. The objective during this phase is to implement the final high-quality integrated INDIA-EMS model across the whole district to achieve 80% population coverage of this model. This rollout will be done primarily by the district administration (the implementation team), with support from the program learning team. The outcome assessment team will conduct the concurrent evaluation and the endline population survey.

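### The endline is specified as one district-wide gain that includes the cluster where the model was developed, so it cannot by itself show whether the finished model works elsewhere

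*Protocol article*

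**What the plan says.** The section on model optimization and development has the first model tested in a "limited sample and geographical setting which is likely to be representative of the entire district". It then gives the selection rule: "A single hub and spoke cluster will be chosen to have a representation of each level of health facility", from prehospital care to Level 4, for each emergency condition. Three iterative cycles lead to the final model Px. Scale-up goes ahead after the third cycle whether or not the threshold set for it has been met.

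Under the heading on scaling up the final model: "The scaling-up sequence will start from the hub and spoke system where pilot testing was conducted and then progressively moved to the other spokes" and to the district's other hubs. The goal of that phase is 80% population coverage across the whole district.

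The endline survey is described under Secondary outcomes. On design: "The sampling strategy and methodology of the endline survey will be similar to the baseline survey". The baseline design is in the Formative research section: "A total of 60 PSUs will be randomly selected", allocated by the district's urban and rural distribution. On purpose: "Objective of the endline survey will be to estimate the increase in population coverage and health facility preparedness as compared to the baseline".

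The article names two ways of splitting results: coverage by emergency condition (Primary outcomes) and incidence by urban and rural area (Quantitative analysis). Neither separates the pilot cluster from the rest of the district.

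**The concern.** The stated aim is a scalable model, and the Discussion lists evidence on effectiveness and scalability among the study's contributions. Scalability asks whether the finished model raises coverage and preparedness in places that did not shape it. The pilot cluster is weak evidence on that: it was selected on purpose, the model was adjusted to what happened there, and it has had the model longest. Yet its catchment lies inside the endline frame, with no stratum and no separate estimate.

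Because scale-up does not depend on the pilot succeeding, the endline carries most of the weight on this question. A single pooled gain could come from a similar rise everywhere, or from a large rise around the pilot hub and little elsewhere. A state deciding on adoption would need to know which.

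**Working it through.** **The plan's own figure.** The baseline sample per district uses a burden of 141/10000, 25% relative precision, 95% confidence and a design effect of one (Formative research).

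n = z²(1 − p)/(p·e²) = 1.96² × 0.9859/(0.0141 × 0.0625) ≈ 4298, against 4292 in the article. Then 4292/0.80 = 5365, rounded up in the article to 6000. The figure is reproduced to within rounding. No pilot quantity enters it, so the sizing does not provide for a separate pilot or non-pilot estimate.

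**What pooling does.** Let w be the share of sampled events arising in the pilot catchment, taken as equal at baseline and endline, and let g_P and g_S be the gains inside and outside it.

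Pooled gain = w·g_P + (1 − w)·g_S

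Pooled gain − g_S = w·(g_P − g_S)

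The article gives none of w, g_P and g_S, so the following values are assumptions. Entries are percentage points by which the pooled gain differs from the gain outside the pilot.

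| w | pilot gains 10 less | equal | pilot gains 10 more | pilot gains 20 more |
|---|---|---|---|---|
| 0.05 | −0.5 | 0 | 0.5 | 1.0 |
| 0.10 | −1.0 | 0 | 1.0 | 2.0 |
| 0.20 | −2.0 | 0 | 2.0 | 4.0 |
| 0.30 | −3.0 | 0 | 3.0 | 6.0 |
| 0.50 | −5.0 | 0 | 5.0 | 10.0 |

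**What separation costs.** If precision follows the number of events, using only the area outside the pilot multiplies the standard error by 1/√(1 − w): 1.05, 1.12, 1.20 and 1.29 for w = 0.10, 0.20, 0.30 and 0.40.

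For power, assume 6000 persons per survey with no non-response, which gives 6000 × 0.0141 = 84.6 events, reduced to 84.6 × (1 − w) outside the pilot. Take a gain d = 0.20 and a two-sided 5% test with n events in each survey. With p̄ the mean of the two coverages p₁ and p₂:

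Power = Φ[(d − 1.96·√(2p̄(1 − p̄)/n)) / √((p₁(1 − p₁) + p₂(1 − p₂))/n)]

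| Baseline coverage | all units (n = 84.6) | w = 0.20 (n = 67.7) | w = 0.50 (n = 42.3) |
|---|---|---|---|
| 10% | 0.91 | 0.84 | 0.64 |
| 20% | 0.82 | 0.72 | 0.52 |
| 30% | 0.76 | 0.66 | 0.47 |
| 40% | 0.74 | 0.65 | 0.45 |

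The article also plans 100 households in each of 60 units with every member included. If 6000 means households, there are more events and power is higher in every cell. The standard-error ratios do not change.

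**The case against.** **The declared target is the whole district.** The pilot is part of the district and is in the frame at both surveys, so a district sample that includes it estimates district coverage correctly. Leaving it out would bias that estimate. This stands in full, and the point does not dispute the 80% figure.

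**A subgroup split can be left to a fuller plan.** In part this stands: pooling is implied by the sampling frame, not stated, and an unseen analysis plan may already contain the split. But the article does name its disaggregations, and the need for this one comes from a design the article itself fixes. The nearest provision, under Geo spatial analysis, is to visualise the effect of different models by spatial and temporal filtering, which is not an estimate.

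**Stronger readings that the article does not support:**

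- *That pooling overstates the effect.* The sign of g_P − g_S is not documented. A pilot area that starts with higher coverage has less room to gain. With a 12-month recall window, areas reached late may contribute events from before roll-out, which would lower their measured gain for reasons unrelated to how well the model works there.
- *That the pilot is the best-equipped part of the district.* The rule asks for every level, including the lowest; in the STEMI example Level 1 has no ECG. Spanning the levels is compatible with the article's expectation that the setting is representative, so that phrase need not be removed.
- *That the pilot had research support and the rest will not.* Table 1 has the support team assisting with both the provisional and the final models, and the pilot cluster also receives Px during scale-up.

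**The non-pilot estimate is less precise.** This stands, and is a reason to read it beside the district figure.

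**Conclusion.** The concern holds as a limit on what the endline can show. The district-wide gain is a sound estimate of district coverage change. It is not a clean estimate of how the finished model performs where it was not developed, and the article specifies no other estimate that is.

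The discrepancy is w × (g_P − g_S), with no documented size or sign. It is zero if the pilot gains what the rest of the district gains, and about 1 to 4 points if the pilot holds 10% to 20% of events and gains 10 to 20 points more. It is negative if the pilot gains less. These figures rest on assumed shares and gains and on a pilot share of events that is the same at both surveys. The change is worth making because the scalability question is the study's own and the separation needs little beyond what is already planned.

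**What to change.** 1. Keep the whole-district estimate as the one for the 80% target.
2. Flag each primary sampling unit and each facility as inside or outside the pilot catchment, using the facility mapping and geo-spatial tagging already planned. Fix the catchment boundary before the endline data are seen.
3. Pre-specify the baseline-to-endline change in coverage and in preparedness separately for the two areas, each with a confidence interval.
4. State that conclusions about scalability rest on the change outside the pilot, read alongside the district figure.
5. When reporting that change, note that the recall window may include events from before roll-out in areas reached late.

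Intervention, sampling method and target stay as they are. The cost is one flag variable, one additional stratified analysis and lower precision outside the pilot. At a 20% pilot share the standard error rises by about 12%. If the survey is 6000 persons, power for a 20-point gain falls from about 0.74–0.91 to 0.65–0.84, depending on baseline coverage. The endline sample size is to be set after the baseline results, so the loss can be weighed then, with the actual pilot share known.
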